### Data collection and documentation in the coordinating center

The linkage between biological samples, questionnaires, and colonoscopy results is established only by the unique participant number. The information collected from colonoscopy and histology reports is entered into an additional standardized study database by trained staff in the coordinating center, using double data entry by two independent and blinded staff members. Data entries are checked for inconsistencies through comparison of the corresponding data sets. In case of differences in data sets, original reports are checked for validation.

Documentation of information collected in the questionnaire and participants’ diary include automated scanning of the questionnaires, optical verification of the scans by trained staff, and comprehensive plausibility checks prior to statistical analysis. All collected information is stored at the coordinating center at least 10 years after the end of the trial.

### Analysis of stool samples

Laboratory analyses of immunochemical FOBGold®Tube Screen test are performed in a blinded manner in an external cooperating laboratory (Limbach Laboratory, Heidelberg). Analyses for the FD Hb/Hp Complex test are performed at the laboratory of the Department of Clinical Epidemiology and Aging Research at the German Cancer research Center in Heidelberg. The FD Hb/Hp Complex quick test enables to test human hemoglobin (Hb) and hemoglobin/haptoglobin complex (Hb/Hp); however, in this trial, only the results from the Hb test will be reported. Both laboratories have extensive experience in the analysis of iFOBTs from previous studies of this group. The iFOBTs used in this trial are commercially available, validated tests. Standard Operating Procedures are established and followed for the analyses.

### Analysis and storage of blood samples

Blood samples are picked up from the study centers by a lab sample transportation service and brought to the coordinating center in Heidelberg. Blood samples are stored at the coordinating center at − 80 °C without a time limit for future development and analysis of biomarkers including genetic markers potentially related to the presence of advanced adenomas and/or colorectal carcinoma and for analysis of the determinants of the effects of acetylsalicylic acid.

As intensive research into new blood tests is continuously ongoing, it is neither meaningful nor possible to explicitly state which exact markers will be tested in the future. Long-term storage of the blood samples collected in this trial will enable timely validation of emerging promising early detection markers in the years to come.

Only the staff of the coordinating center will have access to the samples. However, the samples may be transported to laboratories of cooperating partners (including international partners) for specific analyses.

All laboratory analyses are done in a blinded fashion with respect to both treatment given and clinical/colonoscopy data.

### Quality assurance

The study medication (both acetylsalicylic acid and placebo) is packaged, labeled and blinded according to applicable GCP-V and GMP rules by the Pharmacy of the University Hospital Heidelberg, holding a manufacturing authorization.

There is a responsible investigator in every recruiting study center. The responsible investigator has completed a certified investigator training, including training in ICH-GCP, GCP-V, and AMG (German drug law). The responsible investigator of a study center keeps a confidential list with full names and dates of birth of all participants in the trial, giving reference to the participant’s records. This list is kept in the investigator site file at the study centers. For enrolled participants the date of enrolment and the allocation/randomization number is recorded in this list. The identity of the participants will not be revealed to unauthorized persons.

The participating study centers are visited on a regular basis by qualified staff (visits include an initiation visit, a number of interim visits during the recruitment phase (on-site-monitoring), and a close-out visit). A report is written after each visit.

The steering committee (consisting of the head of the coordinating center, the clinical pharmacology consultant, and the principal investigator of the study (LKP)) meets regularly, either in person or via a telephone conference, to discuss study progress, monitoring reports, and any study-related problems. The conclusions of these meetings are documented.

### Safety assessment

Participants are asked about concurrent use of medication and diseases at inclusion to minimize the risk of AEs. Candidate participants in the trial are excluded if they use potentially interacting medications or have illnesses that may be worsened by participation in this trial. In the patient information documents, participants are informed about all relevant potential AEs that may occur. Furthermore, participants are instructed to contact their general practitioner or the investigator in the unlikely case of a severe medical problem.

The observation period for AEs is defined as day 0 to day 4 for this trial. When the participants come for the scheduled study-independent colonoscopy, they are asked about any potential AEs or events potentially related to the use of the medication. All AEs are documented and the investigator judges intensity, seriousness, and relatedness of an AE using standard criteria. This information is documented in a standardized way in the eCRF. All serious AEs (SAEs) must be reported within 24 h, or on the next working day at the latest, using a standardized SAE report form.

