**Fig. 1 Fig1:**
[figure not shown]
Overview of study flow

**Table 1 Tab1:** Study schedule

Trial-specific procedures	Screening	Baseline	Treat-ment	Observation			Post-study
Timeline			Day 0	Day 2	Day 3	Day 4	Colonoscopy from day 5 onwards
Informed consent	X						
Inclusion/ exclusion criteria	X						
Randomization	X						
Physical examination	X						
Patient parameters^a^	X						
Blood sampling for biomarker analyses (optional)^e^	X						
Questionnaire^b^	X						
Handing over stool collection material and subject diary^c^	X						
Drug administration (Acetylsalicylic acid or placebo)			X				
Stool sample^d^ (FOBGold®Tube Screen)		X		X	X	X	
Stool sample^d^ (FD Hb/Hp Complex)		X		X	X	X	
Concomitant therapy recording			X	X	X	X	
(S)AE recording^f^			X	X	X	X	

^a^Age, sex, weight, height, and blood pressure

^b^The questionnaire includes questions on family history of CRC and lifestyle factors such as smoking and alcohol consumption

^c^Eight kits are handed over

^d^If stool collection on these days is not possible because of constipation or other reasons, stool collection may be postponed to the subsequent days; participants are also allowed to collect only two stool samples, which should be at baseline (without medication) and on day 2, if possible

^e^Blood sampling for biomarker analysis: 2 EDTA tubes; 2 serum tubes

^f^Interview of participants before colonoscopy

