### Colonoscopy

The colonoscopy is planned and conducted in the setting of screening for CRC or diagnostic workup and, as such, it is not part of the trial. However, the investigator must ensure that there are at least 5 days (4 full acetylsalicylic acid-free days) between taking the study medication and the colonoscopy. Although a single dose of acetylsalicylic acid is not considered a contraindication for elective colonoscopy, this time interval was chosen to minimize any possibility of an increased risk of bleeding at colonoscopy or endoscopic removal of small polyps [10–12]. However, the findings from screening colonoscopy are collected and used in the analysis.

Colonoscopy (and histology) reports are de-identified (i.e. any personal data is removed and the participant number is noted) and sent from the study centers to the coordinating center (Division of Clinical Epidemiology and Aging Research at the German Cancer Research Centre, Heidelberg).

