## Appendix

### Full list of inclusion and exclusion criteria

Inclusion criteria

- Age 40 to 80 years (both males and females; premenopausal women must have a negative pregnancy test before inclusion into the trial, postmenopausal women are defined as women who have not had menstrual bleeding for at least 12 months, or have been surgically sterilized)
- Planned screening or diagnostic colonoscopy
- Able to speak and understand German sufficiently to be able to give written informed consent and comply with the trial requirements

Exclusion criteria

- Factors potentially influencing the primary endpoint
  - Diseases/symptoms
    - Chronic inflammatory bowel disease (e.g. Crohn’s disease, ulcerative colitis)
    - Colonoscopy due to positive fecal occult blood test
    - History of colorectal cancer
    - Angiodysplasia of the colon
    - Anamnestic or observed blood loss per anum
  - Use of any of the following drugs
    - Within 2 weeks before the trial
      - Anticoagulants (including, but not limited to heparin, vitamin K antagonists [e.g. phenprocoumon, warfarin], direct thrombin inhibitors [e.g. dabigatran], or factor Xa inhibitors [e.g. apixaban, rivaroxaban])
      - Antiplatelet drugs (e.g. clopidogrel, prasugrel, ticlopidine)
    - Within 1 week before the trial
      - Acetylsalicylic acid
    - Within 3 days before the trial
      - NSAIDs including selective COX-2 inhibitors
- Factors potentially affecting the safety
  - Any current clinically relevant signs and symptoms, including
    - Signs and symptoms suggesting acute peptic ulcer disease
    - Known clinically relevant thrombocytopenia
    - Acute infection
    - Volume deficit (dehydration)
    - Any currently present allergy with dermal reactions, pruritus, or urticaria
    - Severe or insufficiently controlled asthma
    - Severe kidney or liver diseases (e.g. GFR < 30 ml/min, liver cirrhosis)
    - Severe, not sufficiently treated heart failure (as judged by the investigator)
    - Severe, poorly controlled arterial hypertension
    - Any other unclear symptoms needing further investigation in the opinion of the investigator
  - Any of the following anamnestic findings
    - History of severe gastrointestinal bleeding
    - Known hemorrhagic diathesis, including, but not limited to, hypoprothrombinemia, severe thrombocytopenia, hemophilia
    - Asthma, except for patients who have used acetylsalicylic acid in the past without negative effects

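### The stated adverse-event window (day 0 to day 4) ends before any colonoscopy, so bleeding at colonoscopy or polyp removal is not counted by the safety procedures described

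*Protocol article*

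**What the plan says.** Four places in the protocol article bear on this.

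- **Objectives.** The second of the secondary objectives is to study how safe the single dose is in the trial population. Everyone in that population has a colonoscopy planned.
- **Safety assessment.** "The observation period for AEs is defined as day 0 to day 4 for this trial". On arrival for the colonoscopy, participants are questioned: "they are asked about any potential AEs or events potentially related to the use of the medication". SAEs must be reported within 24 hours or by the next working day; no end date is given for that duty.
- **Table 1.** (S)AE recording is marked on days 0, 2, 3 and 4 and not in the post-study column, which reads "Colonoscopy from day 5 onwards". Footnote f, attached to the (S)AE row, reads "Interview of participants before colonoscopy".
- **Colonoscopy.** The investigator must ensure "at least 5 days (4 full acetylsalicylic acid-free days) between taking the study medication and the colonoscopy". The reason given is "to minimize any possibility of an increased risk of bleeding at colonoscopy or endoscopic removal of small polyps". The same section says that a single dose does not rule out elective colonoscopy, treats the procedure as lying outside the trial, and has the colonoscopy and histology reports sent to the coordinating center, where the findings enter the analysis.

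The Statistical analysis section defines the safety population as everyone randomized, whether or not a colonoscopy report is available. It uses the colonoscopy results as the diagnostic reference standard. No safety use of the reports is described.

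**The concern.** The article names a possible harm, adopts a spacing rule to keep it small, and then sets an observation window that closes before the harm could occur. A safety summary produced from that window could not show whether bleeding during or after the procedure differed between the arms.

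This matters for three reasons. Single-dose safety is a declared objective. The abstract's discussion describes the intervention as low-risk and foresees wide use in screening programs, where a positive stool test leads to colonoscopy. And the Impact section states that participants themselves gain nothing from the dose. A reader of the results could take an unremarkable AE table as reassurance about bleeding at endoscopy, although the table was never designed to contain it.

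**Working it through.** The article states no safety figure to reproduce. The main check is one of dates; the arithmetic that follows shows only what a count could deliver.

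**Step 1: dates.**

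| Item | Timing | Source |
|---|---|---|
| AE observation period | days 0 to 4 | Safety assessment |
| (S)AE recording | days 0, 2, 3, 4 | Table 1 |
| AE interview | before colonoscopy | Table 1, footnote f |
| Earliest colonoscopy | day 5 | Table 1; Colonoscopy |

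The last day of the window is 4 and the first possible day of the procedure is 5, so the overlap is zero days. In a participant who follows the schedule, a bleed during the procedure or after polyp removal cannot fall inside the window. The one AE interview described takes place before such a bleed could happen. A colonoscopy later than day 5 widens the gap.

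**Step 2: other routes by which a bleed might be recorded.**

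- Colonoscopy reports reach the coordinating center and are extracted in duplicate under blinding (Data collection and documentation in the coordinating center; Methods against bias). Immediate bleeding might appear in them, but the article describes no extraction or by-arm table of it.
- The SAE reporting rule has no stated end date, but it follows a defined AE period that ends on day 4, and it would not reach non-serious bleeds.
- Delayed bleeding after the visit cannot appear in the report of the procedure, and no later contact is described.

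**Step 3: what a by-arm count could show.** Inputs: 2400 randomized (Screening), equal allocation (Methods against bias), safety set of all randomized (Statistical analysis). Per arm: 2400 / 2 = 1200.

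*No events.* The exact one-sided 95% upper bound is 1 − 0.05^(1/1200) = 0.00249, about 0.25%. The rule of three agrees: 3/1200 = 0.25%. This requires zero events and full follow-up of everyone randomized.

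*Some events.* The documents give no bleeding rate, so a range of 0.1% to 1% is assumed. Expected events per arm are 1200 × 0.001 = 1.2 to 1200 × 0.01 = 12. Approximate power for a doubling, p2 = 2·p1, with a two-sided test at 0.05 and no continuity correction, is

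Φ{ [ |p2 − p1|·√n − 1.96·√(2·p̄(1 − p̄)) ] / √( p1(1 − p1) + p2(1 − p2) ) }, where p̄ = (p1 + p2)/2 and n = 1200.

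| Assumed rate p1 | Expected events in 1200 | Power for a doubling |
|---|---|---|
| 0.1% | 1.2 | 9% |
| 0.3% | 3.6 | 19% |
| 0.5% | 6.0 | 29% |
| 1.0% | 12.0 | 52% |

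A count would therefore be descriptive. It could bound a rate but could not rule out a doubling.

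**The case against.** The strongest reply is that the window was chosen deliberately. The colonoscopy is planned independently, takes place after the trial period, and is called no part of the trial. The protocol regards the risk as small and treats the interval as a precaution. Safety is exploratory, and the primary endpoint, its test and its power do not depend on it. An article also commonly leaves the list of extracted fields, and the handling of late SAEs, to the full protocol, which is not shown.

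Much of this stands. It limits the weight of the point and rules out calling the omission of detail an error. It does not remove the mismatch: the window and the interview timing are stated outright, not left open. The procedure is independent of the trial, but the dose taken before it is the trial's intervention.

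Three stronger readings are tempting and are not supported.

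- *That the exclusion list contradicts the 5-day interval.* Acetylsalicylic acid use is excluded "Within 1 week before the trial", and a reader might infer that the protocol assumes an effect on bleeding that reaches colonoscopies on days 5 and 6. The item stands under factors that could influence the primary endpoint, not under safety. It is a washout protecting the stool-test comparison and says nothing about bleeding at endoscopy.
- *That this is the chief foreseeable harm of the dose.* The article does not rank harms. Its safety exclusions cover many others, such as ulcer disease, asthma and hypersensitivity.
- *That such bleeds could never come to light.* Reports are collected, participants are told to make contact about severe problems, and the SAE rule has no stated end. The accurate statement is that the AE procedures described do not count them.

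**Conclusion.** The point holds as a mismatch between stated passages. The AE window and the colonoscopy period do not overlap, so the safety objective, as currently operationalized, cannot speak to the procedural bleeding that the protocol gives as its reason for the interval. It should be corrected because the correction is cheap, but it is not a defect in the primary analysis.

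The size is modest. With no bleeds among 1200 fully followed participants per arm, the bound would be about 0.25%. A reader might apply the 20% data loss and work with 960 per arm, but that allowance belongs to the sample size calculation, whereas the safety set is everyone randomized. A bound on the rate in one arm also does not measure an excess due to the drug. The power range of about 9% to 52% rests on assumed rates of 0.1% to 1%, which are not in the documents.

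The conclusion assumes that participants follow the schedule and that the full protocol does not set a different window. It concerns data collection only; no view is taken on the dose or on the interval before colonoscopy.

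**What to change.** Reconcile Objectives, Table 1, Colonoscopy and Safety assessment in one amendment.

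1. Define the AE/SAE observation period as day 0 to the end of the colonoscopy visit, and state that bleeding reported to the study center afterwards is recorded. Change Table 1 and its footnote f to match.
2. Add procedural bleeding as a field in the existing blinded double extraction of colonoscopy reports.
3. Tabulate it descriptively by arm, overall and among participants who had polyps removed.
4. If this is not done, state expressly that the safety conclusion covers days 0 to 4 only.

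The cost is an amendment, one extracted field and more AE records, with no added procedure for participants. Some records will be background bleeds from the procedure itself; randomization and blinding make them comparable between the arms. Capture of delayed bleeding will be incomplete because it relies on spontaneous reports, and the result should be presented as descriptive.

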### Methods against bias

The trial is randomized to account for potential confounding factors. Block randomization is used by randomizing participants within blocks such that an equal number is assigned to each treatment (the order in which treatments are allocated in each block is random). Randomization list is compiled with the randomization software RITA – Randomisation in Treatment Arms, Version 1.24, it.e.c.x.

All laboratory tests as well as extraction of clinical data from colonoscopy and pathology reports are done in a blinded manner to avoid information bias. Data extraction and data entry (where applicable) is done by two independent and blinded reviewers. Discrepant coding is resolved according to standard operating procedures to achieve the maximum accuracy possible. In addition, the study centers as well as all participants receive detailed instructions to ensure uniform collection and handling of stool and blood samples. Pre-analysis conditions, including data on storage conditions and duration and mode of transportation, are also documented in detail to control for potential variation.

### Sample size calculation

The sample size is estimated based on the results of the preliminary study including participants from CRC screening with self-reported acetylsalicylic acid use [7]. Accounting for an expected loss of data of about 20% and with an expected prevalence of advanced neoplasms of 10%, 100 advanced neoplasms are expected in each of the two groups. Assuming a sensitivity of 36% in the placebo group (as in our preliminary study) and applying 2-sided chi-square tests with continuity correction at an alpha level of 0.05, this trial should have a power of 90% to detect an increase in sensitivity by short term use of low-dose acetylsalicylic acid to 60% in the entire trial population, and a power of 90% to detect an increase in sensitivity to 70% in gender-specific analyses (sensitivity was 71% in our preliminary study [7]). Furthermore, specificity will be estimated at high levels of precision in both groups, with an expected confidence interval ranging from 88 to 92% for a specificity of 90%.

### Statistical analysis

Standard techniques for the analysis of diagnostic tests will be used [13, 14]. Diagnostic accuracy of the two iFOBTs at the different time points of stool collection will be quantified by estimating sensitivity, specificity, likelihood ratios, positive and negative predictive values (and corresponding 95% confidence intervals) at cut points yielding levels of specificity typically required for routine testing of average-risk populations (> 90%), using the results of colonoscopy as the gold standard. These results will be compared between participants randomized to receive acetylsalicylic acid and those randomized to receive placebo in an intention-to-treat analysis. For the primary endpoint, sensitivity for predefined (test-specific) cut points of test positivity of the FOBGold®Tube Screen test will be compared between users and non-users of acetylsalicylic acid. The stool samples taken on day 2 will be used for these primary analyses.

In addition, the tests will be evaluated over the whole range of cut points by ROC curve analyses and the area under the ROC curve (AUC) will be determined. All analyses will be performed for the total trial population, as well as stratified for gender and separately for the different colonoscopy results (advanced adenomas, defined as presence of at least 1 adenoma with at least 1 of the following features: ⩾1 cm in size, tubulovillous or villous components, high-grade dysplasia, and carcinomas). Analyses will be carried out for stool tests taken at baseline before commencing the study medication and on different days after a single dose of the study drug. Furthermore, analyses will be carried out in which results of tests from stool samples taken on multiple (2 or 3) different days are combined to assess the gain in diagnostic performance by test application on multiple days. Diagnostic performance and its enhancement by acetylsalicylic acid will be evaluated and compared for both of the two iFOBTs employed.

Safety analyses will be performed in the total trial population (i.e. all randomized patients, independent from the availability of stool samples or colonoscopy reports).

The primary endpoints will be analyzed with confirmatory aim; the other statistical analyses will be exploratory.

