### Stool collection

Participants are asked to collect a baseline stool sample before taking the study medication. If the participant cannot collect a stool sample at baseline (e.g. due to constipation), this stool sample is skipped and the study medication is taken without a baseline stool sample. Further stool samples are collected from day 2 onwards on 3 different, preferably consecutive days (day 2, 3, and 4). If stool collection on these days is not possible because of constipation or other reasons, stool collection may be postponed to the subsequent day. Participants are still eligible for inclusion in the analysis if they only provide two stool samples (before taking study medications and on day 2, if possible). At each time point at which stool samples are collected, one kit of each test is used and the actual day documented. The stool sampling devices ensure collection of defined volumes of stool which are given to a buffer that hinders degradation of hemoglobin (for example FOBGold®Tube Screen test: 10 mg stool in 1.7 ml buffer). All stool samples are collected at the participants’ homes and prior to initiation of large bowel preparation for colonoscopy. The stool samples are stored in the refrigerators and sent by mail to the coordinating center (Heidelberg) using special pre-paid and addressed mailing devices.

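### The confirmatory day-2 sensitivity comparison gives no role to the pre-dose FOBGold result, and the only test named is continuity-corrected; adjusting for baseline would gain power at little cost

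*Protocol article*

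**What the plan says.** Under Stool collection, the protocol article states: "Participants are asked to collect a baseline stool sample before taking the study medication". One kit of each of the two tests is used at every collection time, so the baseline sample yields a FOBGold result from the same assay as the primary endpoint. The same section lets a participant who cannot produce a baseline sample skip it and take the study drug anyway.

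Under Statistical analysis, the primary endpoint is FOBGold sensitivity at predefined cut points, compared between the randomized groups, and "The stool samples taken on day 2 will be used for these primary analyses". That section names no test for the comparison. Baseline samples are mentioned separately: "Analyses will be carried out for stool tests taken at baseline before commencing the study medication". Everything beyond the primary endpoints is labelled exploratory.

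The one test that is named stands under Sample size calculation: "applying 2-sided chi-square tests with continuity correction at an alpha level of 0.05". No section gives the baseline result a place as covariate or stratum in the confirmatory comparison.

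**The concern.** Sensitivity is estimated only among participants with advanced neoplasms, so a trial of 2400 answers its confirmatory question with roughly 100 cases per arm. In groups of that size, chance differences in lesion size or in tendency to bleed can move the observed sensitivity noticeably. A pre-dose result of the same assay is the natural variable to absorb such differences, and it is already being collected.

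The planned power refers to a 24-point increase. The article itself gives grounds to consider less. Its Discussion says that the preceding study reflected mostly chronic users, whereas this trial gives a single dose. It also cites another observational study with an increase from 51.2% to 66.7%, which is 15.5 points. Analyses within one sex have about half the cases. In these situations an efficient analysis could decide whether the result is conclusive.

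**Working it through.** **Inputs from the Sample size calculation section.** Two-sided alpha 0.05; placebo sensitivity p1 = 0.36 ("Assuming a sensitivity of 36% in the placebo group"); p2 = 0.60 ("increase in sensitivity by short term use of low-dose acetylsalicylic acid to 60% in the entire trial population"); power 90%; 100 cases per arm; prevalence 10%; data loss about 20%.

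**Step 1: reproduce the plan's figure.** With d = 0.24 and mean proportion 0.48:

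n = [1.960 × √(2 × 0.48 × 0.52) + 1.282 × √(0.36 × 0.64 + 0.60 × 0.40)]² / 0.24² = (1.385 + 0.879)² / 0.0576 ≈ 89 per arm.

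With continuity correction: n' = (n/4) × [1 + √(1 + 4/(n × d))]² ≈ 98 per arm.

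The stated 100 per arm therefore suffices. Exact enumeration at 100 per arm gives 91.6% power for the corrected test. The article's own inputs give slightly fewer cases: 2400 × 0.8 × 0.10 / 2 = 96 per arm, where exact power is 89.8%. The stated 90% is reproduced.

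**Step 2: separate the continuity correction from the baseline.** At 96 per arm and a common sensitivity of 36%, the exact size of the corrected test is 3.5%; without the correction it is just under 5%. Removing the correction therefore raises power with no baseline data at all, and this has to be taken out before any gain is credited to baseline.

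**Step 3: add the baseline.** Baseline and day-2 log-haemoglobin among cases were simulated as bivariate normal with correlation ρ, and day-2 positivity was set by a threshold. The arm term was tested by likelihood ratio in a logistic regression with baseline log-haemoglobin as covariate (4000 runs; Monte Carlo standard error about 0.6 points at 80% power). The documents do not give ρ, so it is an assumption shown over a range.

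| Cases per arm | True sensitivity on ASA (placebo 36%) | Chi-square, corrected (exact) | Chi-square, uncorrected (exact) | Baseline-adjusted, ρ = 0.3 / 0.5 / 0.7 |
|---|---|---|---|---|
| 96 | 60% | 89.8% | 92.1% | about 94 / 96 / 99% |
| 96 | 55% | 71.1% | 75.9% | about 78 / 82 / 89% |
| 96 | 50% | 44.1% | 49.9% | about 52 / 58 / 67% |
| 48 (one sex, equal split assumed) | 60% | 58.8% | 66.7% | about 68 / 74 / 82% |

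At 55%, dropping the correction contributes 75.9 − 71.1 = 4.8 points. Baseline adds about 2, 6 and 13 points beyond that. At ρ = 0 the adjusted test has about 76% power, the same as the uncorrected crude test.

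**Step 4: a simpler adjustment.** A Mantel-Haenszel test stratified by baseline positive or negative, without continuity correction, gives about 77 / 80 / 86% at 55% for the same ρ. That is less than the continuous covariate, but part of the gain remains.

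**Step 5: validity and skipped baselines.** With 10% of baselines assumed missing and coded as their own category, power at 55% stays at about 77 / 83 / 89%, and rejection under the null is 0.050 to 0.055. The baseline sample is taken after randomization but before the blinded dose, so the treatment cannot influence it.

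**The case against.** The strongest reply is that nothing is wrong. The Statistical analysis section names no test, and a simple test is often used for sizing even when the final model has covariates. A statistical analysis plan that is not shown could contain the adjustment. The crude comparison is valid under randomization, estimates the marginal sensitivity of a single day-2 test directly, needs no model and reaches its stated power. All of this stands. It limits the point to efficiency, but does not remove it: the article fixes the time point and labels baseline analyses exploratory, and the one test it names has no covariate.

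Three stronger readings are tempting, and the documents do not support them:

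- A reader might infer that every case has a pre-dose value. The Stool collection section allows the sample to be skipped.
- A reader might credit the whole distance from 71% to the adjusted figures to baseline. About 5 points of it come from dropping the continuity correction; at ρ = 0.3 that is more than baseline itself adds.
- A reader might conclude that the trial is underpowered. At the article's own 36% versus 60% it is not.

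**Conclusion.** The point holds as a recommendation to improve efficiency. The planned comparison is sound and has about 90% power at its design effect, where there is little left to gain. For a smaller true effect, or within one sex, the named test gives up power. At 36% versus 55% with 96 cases per arm, this is about 5 points through the continuity correction and a further 2, 6 or 13 points through leaving baseline out, at ρ of 0.3, 0.5 or 0.7.

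The first part is exact arithmetic. The second rests on an assumed correlation and a bivariate normal model, and it vanishes at ρ = 0. That the primary analysis is unadjusted is itself inferred from the sample size section, since no test is stated for the comparison.

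**What to change.** Before unblinding, specify the primary analysis among participants with advanced neoplasms as day-2 FOBGold positivity by randomized arm, adjusted for the baseline FOBGold result and without continuity correction. Either of two forms will do:

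- logistic regression on arm and baseline log-haemoglobin, with a missing-baseline category and a likelihood-ratio test of the arm term; or
- a Mantel-Haenszel test stratified by baseline positive, negative or missing.

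In both cases, report the standardized (marginal) sensitivity difference with its 95% confidence interval, so that the quantity of interest does not change to a conditional odds ratio. Keep the crude 2x2 comparison as the sensitivity analysis.

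The change needs no further participants or samples. It costs a few lines of text and code, a simple model in place of a 2x2 table, and a stated rule for skipped baselines. It has to be fixed in advance: if chosen after unblinding, the adjusted result could not carry the confirmatory claim.
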